### Aims

The first aim of the study is to determine the feasibility of the intervention, including its acceptability, and further refine intervention materials and study procedures (recruitment, enrollment, intervention, retention, and data collection). The second aim of study is to test the effects of the intervention on maternal outcomes from baseline at 22–36 weeks pregnant (Time 1) to 6 weeks postpartum (Time 2), 4 months postpartum and completion of Phase I (Time 3), 7 months postpartum and completion of Phase II (Time 4), and 10 months postpartum, after 3 months on their own (Time 5). The primary maternal outcome is a decrease in fasting blood glucose and weight from baseline to 10 months postpartum. Secondary maternal outcomes include a decrease in glucose levels from the oral glucose tolerance test, insulin levels, homeostatic model assessment of insulin resistance (HOMA-IR), glycated hemoglobin A1C (A1C), lipid panel, blood pressure, and adiposity, as well as improvement in health behaviors, eating, exercise and breastfeeding self-efficacy from baseline to 10 months postpartum. The third aim of the study is to quantify the effects of the intervention on infant feeding and growth outcomes (weight status [weight-for-length]) and breastfeeding (weeks until stopped breastfeeding, weeks exclusively breastfed, and intensity of breastfeeding) from birth to 10 months postpartum.

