### Infant outcomes

For infant feeding and growth (Aim 3), we will measure breastfeeding duration and intensity as a modifiable risk factor for maternal and infant metabolic disease. We will define breastfeeding duration as the time since birth, in weeks, until the mother stops breastfeeding or expressing milk for her infant. We will define exclusive breastfeeding as the time, in weeks, until the mother introduces formula or complementary foods. We will define breastfeeding intensity as the percent of all milk feeds that are breast milk (# of breast milk feeds per day) / (# of breast milk + formula + other milk feeds per day) [73,74]. We will measure weight-for-length in infants, using standardized weight-for-length z scores [75]. Length will be measured twice and averaged using a portable length board and weight will be measured twice and averaged using a portable calibrated digital scale according to procedures.

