For each outcome mentioned in **Aims 2 and 3**, a separate linear mixed-effects model will be constructed. These will model data across all available post-baseline time points; contrasts will be constructed to evaluate the effects of the intervention over the post-baseline period, as compared to the wait-list control group, with covariate adjustment for baseline values. These models will include assessment for main effects for experimental group, time point, and site, as well as interactions, and will account for the within-site and within-subject correlation structure invoked via the study design. This approach will provide useful information in guiding the analysis of a future study. Least-squares means will be computed and plotted for each time point for each group to determine average trajectories for each measure.

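### Two breastfeeding durations, each a single time from birth to an event, are assigned to a baseline-adjusted repeated-measures linear mixed model that does not fit them

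*Protocol article*

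**What the plan says.** In the protocol article, the Aims section lists "weeks until stopped breastfeeding, weeks exclusively breastfed, and intensity of breastfeeding" among the Aim 3 outcomes, followed from birth to 10 months postpartum. The Infant outcomes section fixes the first two as times to an event: "We will define breastfeeding duration as the time since birth, in weeks, until the mother stops breastfeeding or expressing milk for her infant", and "We will define exclusive breastfeeding as the time, in weeks, until the mother introduces formula or complementary foods".

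The Data analysis section (Aims 2 and 3) then prescribes one approach for every outcome of both aims: "a separate linear mixed-effects model will be constructed". It adds "These will model data across all available post-baseline time points", that "contrasts will be constructed to evaluate the effects of the intervention over the post-baseline period", and that this is done "with covariate adjustment for baseline values". Main effects and interactions of group, visit and site are included, and least-squares means are computed per visit and group. No exception is made for the durations, and no time-to-event method or censoring rule is named.

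Table 2 schedules both durations at Times 2, 3, 4 and 5, with no entry at Time 1. Its footnote ends collection of the breastfeeding items once a mother stops. The Power analysis section expects 20% attrition.

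**The concern.** A linear mixed model for repeated measures suits a quantity that is observed afresh at each visit. These two durations are not of that kind. Each woman has one value, and at any visit before the event only a lower bound is known.

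Four features of the stated model do not fit:

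- **Cap at the visit time.** A woman who has not had the event by 6 weeks can contribute at most 6 weeks at Time 2, whatever her eventual duration.
- **Censoring.** Women still breastfeeding at Time 5, and women who drop out earlier, have incomplete durations. The linear model would treat them as complete.
- **Rows that end because of the outcome.** If the footnote means that no row exists after stopping, later rows are missing because of the outcome itself.
- **No baseline.** Neither duration can have a value before birth, so the baseline adjustment cannot be applied. This is a supporting point only: infant weight-for-length has no Time 1 entry either.

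Breastfeeding support is a core part of the intervention, Aim 3 is to quantify its effect on infant feeding, and the models are meant to guide a later study. An effect in weeks that is not the difference in duration could mislead the planning of that study.

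**Working it through.** **Plan figures.** The article gives no effect size, median or power specific to these outcomes. Its attrition figure reproduces: 80 / (1 − 0.20) = 100. Its power statement is in SD units (0.67 SD for .80) and does not bear on this point.

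**Assumptions, none given in the article.** Durations are exponential; a woman still breastfeeding is recorded at weeks so far; a woman who has stopped keeps her duration at later visits; the contrast weights the four visits equally. There is no dropout and no clustering.

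**Visit times.** 6 weeks, then 4, 7 and 10 months at about 4.35 weeks per month: 6, 17.4, 30.4 and 43.5 weeks.

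**Formula.** With λ = ln 2 / median, the expected weeks recorded by time t are (1 − exp(−λt)) / λ, and the proportion still breastfeeding is exp(−λt).

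**Worked example, medians 20 (control) and 30 (experimental).** The values of 1/λ are 28.85 and 43.28 weeks. At 43.5 weeks, 22% and 37% are still breastfeeding. Expected weeks at Time 5 are 28.85 × (1 − 0.221) = 22.46 and 43.28 × (1 − 0.366) = 27.44, a difference of 4.97 allowing for rounding.

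| Visit | Weeks | Arm difference (weeks) |
|---|---|---|
| Time 2 | 6 | 0.19 |
| Time 3 | 17.4 | 1.26 |
| Time 4 | 30.4 | 3.05 |
| Time 5 | 43.5 | 4.97 |
| Equal-weight average | | 2.37 |

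The average is 2.37 / 4.97 = 48% of the difference to 10 months.

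**Range.** Over control medians of 12 to 35 weeks and hazard ratios of 0.5 to 0.75, the average is about 45–53% of the 10-month difference. Still breastfeeding at 10 months are 8–42% of controls and 15–65% of the experimental arm.

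**Standardized effect.** Averaging also shrinks the SD. For medians 20 and 30 the effect is 0.32 SD at Time 5 and 0.30 SD for the average. For medians 20 and 40 it is 0.53 and 0.49.

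**Power.** Simulation with 40 per arm, two-sided 0.05, hazard ratio 0.5 and months taken as 4.33 weeks:

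| Control median (weeks) | Log-rank, censored at 43 weeks | Visit-averaged contrast |
|---|---|---|
| 12 | 0.81 | 0.72 |
| 20 | 0.70 | 0.56 |
| 26 | 0.63 | 0.49 |

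Type I error was 0.047–0.058 for both methods.

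**If rows end when the mother stops.** An exchangeable GEE with a group-by-visit term was used as a stand-in for the mixed model (250 runs, hazard ratio 0.5). For control medians 12 / 20 / 26, the estimated contrast falls from 4.4 / 3.6 / 3.3 weeks to 1.3 / 0.8 / 0.7 weeks, with power about 0.52 / 0.48 / 0.46.

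**The case against.** The strongest reply is that the plan already produces a usable figure. It computes least-squares means and standardized effect sizes at each visit and allows interactions. The word contrasts is plural and no weights are given, so an equal-weight average is only one possible reading. If weeks so far are recorded and nobody drops out, the Time 5 arm difference is exactly the difference in restricted mean weeks to 10 months, which is one of the remedies proposed below. That stands. It holds, however, only if women who stopped keep their recorded duration and dropouts are handled as censored. The article says neither, and the footnote and the 20% attrition point the other way.

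A reader might infer that censoring in itself biases the comparison toward zero, or that half the evidence is lost. The documents do not support this. Censoring at a common 10-month limit gives no bias for a difference defined to 10 months, and that is the period the Aims section names. The halving in weeks is mostly a change of scale, since the standardized effect barely moves.

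A reader might also apply the 22% and 37% still breastfeeding to both outcomes. They describe time to stopping. Exclusive breastfeeding ends at first formula or complementary food, so few women may be censored at Time 5; there the cap at earlier visits and dropout matter more.

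It is also fair that these are Aim 3 outcomes in a feasibility design, and that an article may leave model details to an analysis plan. But the article is not silent here: it assigns a model to these outcomes, and that model does not fit their definitions.

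**Conclusion.** The point holds as a mismatch between a stated method and two stated outcome definitions, and it should be corrected. A contrast averaged over Times 2 to 5 does not estimate the difference in duration to 10 months. Under the exponential assumptions it is about 45–53% of that difference in weeks, and could be less if rows end at stopping. The cost in evidence is moderate: a small loss in standardized effect, some loss of power against a log-rank test, and type I error near 5%.

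These sizes rest on assumed distributions, medians, hazard ratios and coding rules, without dropout or clustering. The mismatch itself rests on the text alone. It does not extend to breastfeeding intensity or weight-for-length z scores, which are true repeated measures, and it does not touch the primary maternal outcomes.

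**What to change.** Exempt weeks until breastfeeding stopped and weeks exclusively breastfed from the mixed-model sentence, leaving intensity and weight-for-length z scores under it. For each of the two:

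- Use one record per woman: time from birth to stopping, or to first formula or complementary food, censored at last contact or at Time 5.
- Show Kaplan-Meier curves by arm.
- Estimate the arm effect as the difference in restricted mean weeks to 10 months, or by a Cox model, adjusted for site and allowing for the randomized enrollment groups.
- Drop the baseline adjustment for these outcomes, and state that the footnote to Table 2 ends further questions but keeps the recorded duration.

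This changes analysis wording and adds a little analysis work. Both durations are already defined in weeks since birth. The article lists weeks and does not mention stop dates, so the team should confirm that the week of each event is recorded. The main limitation is the small number of clusters: two sites with four enrollment groups each give eight randomized groups, so the variance estimate needs a small-sample method and will remain imprecise.

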**Self-Efficacy Outcomes**						
Eating Self-Efficacy Scale	Mothers	X	X	X	X	X
Exercise Self-Efficacy Scale	Mothers	X	X	X	X	X
Breastfeeding Self-Efficacy Scale	Mothers	X	X	X	X	X

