**Aim: 3 Infant Feeding and Growth**						
Weeks until breastfeeding stopped ^#^	Mothers		X	X	X	X
Weeks exclusively breastfed ^#^	Mothers		X	X	X	X
Intensity of breastfeeding ^#^	Mothers		X	X	X	X
Weight-by-Length Z scores	Infants		X	X	X	X
**Demographic Data**	Mothers	X				

T1 (Baseline, at 22–36 weeks); T2 (6 weeks postpartum); T3 (4 months postpartum at completion of Phase I); T4 (7 months postpartum at completion of Phase II); T5 (10 months postpartum, after 3 months on their own); ^1^ 3 hour OGTT performed as part of GDM diagnosis includes fasting, 1, 2, and 3 hour glucose after a 100 g load; ^2^ 2 hour OGTT includes a fasting and 2 hour glucose after a 75 g glucose load; * Not done pregnant; ^#^ If a mother stops breastfeeding we will stop collecting data.

To assess acceptability of the intervention (Aim 1), the project manager will observe two randomly selected sessions per month to assess whether the sessions are being taught by the protocol. Participants will be asked to complete an evaluation at the completion of each session. At the Time 5 data collection, a trained research assistant will conduct a 15-minute exit interview with all experimental group women. To assess other aspects of feasibility, the project manager and research assistants will keep screening and enrollment logs on recruitment efforts; the number who were ineligible, with reasons for ineligibility; and the number who declined to participate with reasons why. The interventionists will keep field notes and collect data on attendance at each session, reasons for non-attendance, and number of make-up sessions provided. To assess the feasibility of the instruments, the research assistants will keep field notes and collect data on length of time it takes participants to complete each instrument, challenges encountered, and the ways they were resolved.

For maternal outcomes (Aim 2), research assistants blinded to the study group assignment will collect all data. The research assistants will use a standardized manual for collecting physiological and questionnaire data. Prior to each data collection, the research assistants are tested for inter-rater reliability on height, weight, waist circumference, triceps and subscapular skinfolds, and weight-for-length measurements.

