### Data analysis

#### Aim 1

To determine the acceptability of the intervention sessions and materials, the investigators will analyze the interventionists’ field notes and exit interviews with women, which will be tape-recorded with participants’ permission, transcribed, and analyzed for themes. The findings will be used to further adapt and refine the intervention*.* To assess other aspects of feasibility, recruitment yield will be described by the number contacted and the number screened required to yield one enrollment. Interventionists will keep attendance records for each class. Retention will be described at each time point. Statistics on data collection, such as duration of collection per woman, will also be computed at each time point. Rates of recruited, screened, and retained women will be presented by group and time point, along with 95% confidence intervals; the upper bounds will provide an estimate of worst case values for rates in a future study.

#### Aims 2 and 3

To analyze maternal outcomes, descriptive statistics will be calculated for each measure at each time point. All analyses will be conducted using an intention-to-treat approach. Standardized effect sizes for each measure will be calculated for each time point as the ratio of the mean difference between the intervention and wait-list control group to its standard deviation. Correlation matrices will be computed to describe the degree of correlation of each measure across the repeated measures for each group. For the assessment of trends in Aim 2, preliminary analyses will be conducted to determine whether, despite randomization, the intervention and control groups were unbalanced at baseline on any measured variable. Any such variable will be examined for statistically significant relationships with any of the outcome measures, and if any are found, the variable will be considered as a covariate for subsequent models.

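### Baseline adjustment is promised for every Aim 2 and Aim 3 outcome, but five of them have no Time 1 value; for breastfeeding, a prenatal covariate already collected should be named in advance

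*Protocol article*

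**What the plan says.** Under Data analysis, Aims 2 and 3, the protocol article says that for each outcome in those aims "a separate linear mixed-effects model will be constructed", fitted to all available post-baseline time points "with covariate adjustment for baseline values". The models also contain group, time point, site and interactions.

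The Aims section lists infant weight-for-length and three breastfeeding outcomes under Aim 3: "weeks until stopped breastfeeding, weeks exclusively breastfed, and intensity of breastfeeding". Under Infant outcomes, breastfeeding duration is "the time since birth, in weeks, until the mother stops breastfeeding or expressing milk for her infant"; exclusive breastfeeding is likewise a time in weeks, ending when formula or complementary food is introduced. Table 2 marks all three breastfeeding outcomes and the infant z score at Times 2 to 5 only. It marks maternal waist circumference, an Aim 2 outcome, as not done in pregnancy.

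Table 2 also marks the "Breastfeeding Self-Efficacy Scale" for mothers at every time point, Time 1 included.

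One other passage brings in covariates: "For the assessment of trends in Aim 2, preliminary analyses will be conducted" to look for baseline imbalance between the groups. An imbalanced variable that is also significantly related to an outcome is then to be considered as a covariate in later models.

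**The concern.** The promise of baseline adjustment covers every outcome, but for five of them there is nothing to adjust for. The plan neither carves out these outcomes nor names a substitute, so whoever fits the models must decide after the data are in whether to use a covariate and which one.

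This matters most for breastfeeding. It is what the intervention works on before 6 weeks postpartum, through the prenatal class and the weekly calls. Only eight groups of women are randomized, so prenatal breastfeeding confidence may differ between arms by chance. A score that could absorb some of that difference, and some outcome variance, is already scheduled for every woman. At stake are precision, protection against chance imbalance, and freedom from a data-driven choice of covariate.

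**Working it through.** **Which outcomes lack a Time 1 value (Table 2)**

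| Outcome | Aim | Time 1 | First value |
|---|---|---|---|
| Weeks until breastfeeding stopped | 3 | none | Time 2 |
| Weeks exclusively breastfed | 3 | none | Time 2 |
| Breastfeeding intensity | 3 | none | Time 2 |
| Infant weight-for-length z score | 3 | none | Time 2 |
| Maternal waist circumference | 2 | none | Time 2 |
| Breastfeeding self-efficacy (candidate covariate) | 2 | yes | Time 1 |

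For the four Aim 3 outcomes a Time 1 value cannot exist, because the child is not yet born.

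**Is the Time 1 self-efficacy score a proper baseline covariate?** Controls follow the same Time 1 to Time 5 schedule (Design). Procedures places questionnaires at the enrolment visit after consent. Settings and Power analysis place allocation after each enrolment period, once a group has been inducted. So the score should precede allocation. This is an inference from three sections; no sentence says it of this scale.

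**The plan's own power figures.** Inputs: 40 completers per group, two-sided 0.05, effects of 0.67 and 0.8 SD, and 2 sites × 4 enrolment groups = 8 groups, so 80/8 = 10 completers each. No intracluster correlation (ICC) is given. A two-sample t calculation on 78 degrees of freedom, with variance multiplied by 1 + (10 − 1) × ICC, gives:

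| ICC | Power at 0.67 SD | Power at 0.8 SD |
|---|---|---|
| 0 | 0.841 | 0.942 |
| 0.01 (assumed) | 0.809 | 0.923 |
| Stated in the plan | 0.80 | 0.92 |

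The stated figures are thus reproduced with an ICC of about 0.011 to 0.013. No stated number is in dispute.

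**Gain from the covariate.** Let r be the correlation between the Time 1 score and the breastfeeding outcome. The document gives no value; 0.2 to 0.5 is assumed. Residual variance is multiplied by 1 − r², the equivalent gain in women is 1/(1 − r²) − 1, and the effect detectable with 0.80 power is 0.67 × √(1 − r²). Power starts from the stated 0.80, which implies a design effect of 1.116.

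| r | Fall in residual variance | Equivalent gain in women | Power at 0.67 SD | Detectable effect (SD) |
|---|---|---|---|---|
| 0.2 | 4% | 4% | 0.816 | 0.656 |
| 0.3 | 9% | 10% | 0.836 | 0.639 |
| 0.4 | 16% | 19% | 0.864 | 0.614 |
| 0.5 | 25% | 33% | 0.899 | 0.580 |

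This assumes a linear model and the same proportional reduction in variance within and between groups.

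**Chance imbalance at Time 1.** With 50 women per arm in groups of 100/8 = 12.5, the standard error of the standardized arm difference is √(2 × D/50), where D = 1 + 11.5 × ICC.

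| ICC | D | Standard error | Chance of a difference above 0.3 SD, either direction |
|---|---|---|---|
| 0 | 1.000 | 0.200 | 13% |
| 0.0129 (implied by the stated power) | 1.148 | 0.214 | 16% |
| 0.05 (assumed) | 1.575 | 0.251 | 23% |

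An imbalance of 0.3 SD would move the unadjusted breastfeeding contrast by 0.3 × r, that is 0.06 SD at r = 0.2 and 0.15 SD at r = 0.5.

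**The case against.** A reader might infer that the breastfeeding comparisons will go wholly unadjusted, or will be biased. The documents support neither. The models keep site and time point. The imbalance screen sits under a heading that covers Aims 2 and 3, takes in any measured variable, and feeds later models, which include those for Aim 3. Breastfeeding self-efficacy is itself an Aim 2 outcome with a Time 1 value, so an imbalanced score could enter by that route. Randomization protects the contrast from systematic bias; what remains is chance error. These points stand, and they limit the claim.

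They do not close the gap. The screen is introduced for Aim 2, needs both an observed imbalance and a significant association, and even then leaves inclusion open. A covariate chosen that way is weaker than one fixed in advance, and it gives no precision when the arms happen to be balanced.

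It can also be said that naming a covariate for a non-primary outcome in a feasibility trial belongs in the analysis plan, and that the sensible reading is to adjust where a baseline exists. That would answer a complaint about missing detail. Here, however, the article states a rule without exception that its own measurement table makes impossible for five outcomes.

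The size is open to challenge: it rests wholly on an assumed r. At 0.2 to 0.3 power rises only to 0.816 to 0.836, and a shift of 0.06 to 0.15 SD is small beside 0.67 SD. The document also does not show that self-efficacy predicts breastfeeding better than any other Time 1 variable; its social cognitive framework only makes it a natural choice.

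**Conclusion.** The point holds as an inconsistency between the analysis text and Table 2, with a nearly free improvement attached. Own-baseline adjustment cannot be carried out for the three breastfeeding outcomes, infant weight-for-length or waist circumference, and no substitute is fixed.

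The benefit of the remedy for breastfeeding is better precision and protection against chance imbalance: modest at the low end of the assumed correlations and worthwhile at the high end. It depends on the assumed r, on a linear model, and on the inference that Time 1 questionnaires precede allocation. If duration or exclusivity is analysed by another model form, the covariate remains sensible but the percentages need not carry over. The primary outcomes, fasting glucose and weight, have Time 1 values and are not affected.

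**What to change.** In the model paragraph under Data analysis, Aims 2 and 3:

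1. Limit own-baseline adjustment to outcomes measured at Time 1.
2. Prespecify the Time 1 Breastfeeding Self-Efficacy Scale score as covariate for breastfeeding duration, exclusivity and intensity, regardless of any imbalance test.
3. State which Time 1 covariate, if any, applies to infant weight-for-length z score and to maternal waist circumference.

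Confirm in the same place that the Time 1 questionnaires are completed before allocation is known. The cost is a few sentences and one degree of freedom per model; no new data are needed.

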### Settings

The study is being conducted in partnership with the University of North Carolina at Chapel Hill (UNC-CH) Schools of Nursing and Medicine and two clinical sites, Rex Healthcare and WakeMed. Our team has had a longstanding relationship with both sites. A local church near Rex Healthcare and a community center near WakeMed are being utilized for enrollment, data collection and delivery of the intervention. Women will be enrolled during four enrollment periods. After each of the four enrollment periods, the sites will be randomized to the experimental or wait-list control group. Women will be told their group assignment by phone.

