### Power analysis

Eighty women are expected to complete the study; 40 per group. We will induct 100 women to take into account a 20% attrition rate seen in our previous studies [37-39,53]. While individually randomizing women to either the experimental or wait-list control group would be ideal, this is not feasible in our settings because of the limited number of women with GDM available in each site during any given enrollment period. Therefore, we have chosen a cluster-randomized approach. After a group of women is inducted, they will be randomly assigned to either the experimental group or the wait-list control group, to provide a balanced allocation in each site, yielding a random sequence of two experimental groups and two wait-list control groups for each site. This will provide two-group, longitudinal comparisons of complete data on 40 women per group, for analyses of changes in metabolic, clinical, weight, adiposity, health behaviors, and self-efficacy at up to four post-baseline time points. A cluster power calculation was performed with POWERLIB20 SAS/IML modules, which incorporate the methods described in Muller [54]. These methods calculate power for the general linear multivariate model, including repeated measures data, allowing adjustment for within-cluster correlation, which is expected to be small. We intend to determine effect size for each maternal and infant outcome addressed in Aims 2 and 3 in separate multivariate models. The study will be well powered to detect moderate to large effect sizes. An effect size of .67 SD at any post-baseline time point with this sample size will provide .80 power at the two-sided .05 significance level; an effect size of .8 SD increases the power to .92.

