### Phase I intensive intervention

The Phase I classes are adapted from *Children and Parents Partnering Together to Manage their Weight*[56] and the feasibility study *Reducing the Risk of Chronic Disease: A Group- Based Weight Loss Program for Postpartum Mothers*[57] with additional sessions about 1) the importance of breastfeeding for metabolic control and infant health and 2) reinforcement of GDM reoccurrence with future pregnancies, and progression to prediabetes and T2DM [37-39,53]; and weekly educational and motivational text messages until women have completed their time in the study. Each 60-minute session will be delivered to a group of 12–13 women (Table 1). All women at both sites receive a GDM education class at the time of diagnosis by a certified diabetes educator. These existing classes are virtually identical. We have added two classes. We will deliver the first class during pregnancy, on the benefits of breastfeeding for metabolic control and for infant health. We will deliver the second class when women are 6 weeks postpartum to reinforce knowledge of recurrent GDM and progression to T2DM. To further support breastfeeding, our interventionists, who have experience in breastfeeding support, will contact experimental women weekly until they start classes (6 weeks postpartum) to inquire how breastfeeding is progressing and answer questions using a protocol we have developed with a consultant for our study, based on an effective pre- and post-natal breastfeeding intervention protocol [58]. We have a lactation consultant on the grant that will be available to assist with mother’s breastfeeding concerns. Also, at each site, registered dietitians will be available to discuss caloric needs with breastfeeding mothers in the experimental group [59].

**Table 1 T1:** Phase I intensive intervention

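### The mixed models name site and subject as correlation levels but not the randomised cohort; if the cohort ICC is positive, arm-effect standard errors are too small and type I error exceeds 5%

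*Protocol article*

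**What the plan says.** All places are in the protocol article.

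- **Unit of allocation.** The Power analysis section explains that individual randomisation is not feasible: "Therefore, we have chosen a cluster-randomized approach. After a group of women is inducted, they will be randomly assigned" as a group to one arm or the other, "yielding a random sequence of two experimental groups and two wait-list control groups for each site". The Settings section names "two clinical sites, Rex Healthcare and WakeMed" and states: "After each of the four enrollment periods, the sites will be randomized to the experimental or wait-list control group".
- **Group size.** Under Phase I intensive intervention: "Each 60-minute session will be delivered to a group of 12–13 women".
- **Numbers.** "Eighty women are expected to complete the study; 40 per group", and "We will induct 100 women to take into account a 20% attrition rate". Stated power is .80 for an effect of .67 SD and .92 for .8 SD, two-sided at .05. The calculation is said to allow for within-cluster correlation, described only as small.
- **Analysis model.** Under Data analysis, Aims 2 and 3, each outcome gets a linear mixed model with main effects of arm, time point and site, plus interactions, adjusted for the baseline value. The model "will account for the within-site and within-subject correlation structure invoked via the study design". No term for cohort or enrollment period is listed.

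**The concern.** The arm comparison is a comparison between cohorts, so its error variance must include cohort-to-cohort variation. Women in one cohort share an allocation and a calendar period. In the experimental arm they also appear to share a class and an interventionist during follow-up. If the model recognises only site and subject, it treats women within a site as independent, and the precision of the arm effect is overstated.

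This matters because Aim 2 sets out to test effects on maternal outcomes, including the primary ones, and the same model form serves all Aim 2 and Aim 3 outcomes. The article also offers this modelling as a guide to the analysis of a future study. A model without a cohort level would not estimate the cohort ICC that such a study would need.

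**Working it through.** **1. Number and size of randomised units.** 2 sites × 4 periods = 8 cohorts, with 2 per arm at each site and so 4 per arm overall. Enrolled: 100/8 = 12.5 per cohort, which matches the stated group size. Completers: 80/8 = 10 per cohort. The enrolment figure follows from 80/(1 − 0.20) = 100.

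**2. The article's power figures.** With 40 per arm and independent women, the standard error in SD units is √(2/40) = 0.2236.

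- At .67 SD: .67/0.2236 − 1.96 = 1.04, power .850 (normal) or .841 (t, 78 df).
- At .8 SD: .8/0.2236 − 1.96 = 1.62, power .947 (normal) or .942 (t, 78 df).

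These exceed the stated .80 and .92. With a design effect DE = 1 + (10 − 1) × ICC, setting power at .67 SD to .80 gives ICC ≈ .016 (DE 1.144, normal) or ≈ .013 (DE 1.116, t with 78 df). Either value then gives .917 at .8 SD, which agrees with .92. Because the ICC is back-solved, this shows consistency with the stated figures and does not reproduce them.

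**3. Why site does not stand in for cohort.** Each site contributes two cohorts to each arm, so a site effect, fixed or random, cancels from the arm contrast. Cohort effects do not cancel. An arm-by-site term does not help, because each arm-by-site cell still pools two cohorts.

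**4. Type I error if cohort is ignored.** Formula: 2 × [1 − Φ(1.96/√DE)] with 10 per cohort. For example, at ICC .016, 1.96/√1.144 = 1.83, giving 6.7%. The simulation used 8 cohorts of 10, with two per arm randomised within each site, one post-baseline time point, no baseline covariate and 20,000 runs per ICC.

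| Assumed ICC | DE | Formula | Simulated, arm + site | Simulated, with arm × site | Cohort means, 5 df |
|---|---|---|---|---|---|
| 0 | 1.00 | 5.0% | 5.3% | 4.9% | 5.0% |
| .01 | 1.09 | 6.1% | 6.4% | 5.9% | 5.2% |
| .016 | 1.14 | 6.7% | 6.7% | 6.6% | 5.3% |
| .05 | 1.45 | 10.4% | 10.5% | 10.4% | 5.1% |
| .10 | 1.90 | 15.5% | 16.2% | 16.6% | 5.0% |

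With 12.5 per cohort instead of 10, the formula gives 6.3%, 7.2%, 11.8% and 18.1% at ICC .01, .016, .05 and .10.

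**5. Standard errors (arm + site model).** At ICC .016 the mean model standard error is 0.222 against a true 0.240, so 7% too small. At ICC .05 it is 0.221 against 0.271, so 18% too small.

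**6. Degrees of freedom and power once cohort is recognised.** Between-cohort df are 8 − 2 = 6 with arm alone, 8 − 3 = 5 with arm + site, and 8 − 4 = 4 if arm × site is kept. Power by non-central t:

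| ICC | df | .67 SD | .8 SD |
|---|---|---|---|
| 0 | 6 | .71 | .84 |
| 0 | 5 | .67 | .81 |
| .016 | 6 | .65 | .80 |
| .016 | 5 | .62 | .76 |

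The article's .80 and .92 are not reached on these df, even with no cohort correlation.

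**The case against.** **The wording may already include cohort.** The model sentence appeals to the correlation that the design creates, and the Power analysis section calls that design cluster-randomised. The Settings section itself uses the word site for the unit that is randomised after each period. In a condensed article, within-site could be loose wording for within site-and-period cohort. This has some force: a reader should not infer that the investigators overlooked clustering or decided to ignore it, since the power section allows for it. It does not dispose of the point. The same passage of the analysis section lists site as a main effect, where it can only mean the two sites, and neither cohort nor period appears anywhere in the model. An analyst following the text would leave the randomised unit out.

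**The ICC is expected to be small.** This stands as a limit on size. At ICC 0 there is no inflation, and the power figures point to roughly .013–.016. A reader might take the 10–16% error rates as the trial's expected behaviour. The article does not support that, because those rates need ICCs of .05 to .10.

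**Shared classes do not apply to both arms.** A reader might infer that every cohort is correlated through a common class and interventionist. Control cohorts receive usual care and are offered classes only after Time 5, so this source can act only in experimental cohorts during follow-up. Shared allocation and calendar period remain in both arms. A single common ICC is therefore a simplification.

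**The calculations are not the planned model.** This is also fair. The plan has repeated post-baseline measures and baseline adjustment, and the effective ICC under that model is unknown and will differ by outcome.

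**It is a feasibility study.** The Design section does frame it so, but Aim 2 tests effects and power is stated for a two-sided .05 test.

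**Conclusion.** The model as written omits the level at which treatment is allocated, and the site terms it does contain cannot replace that level. If the cohort ICC is positive, arm-effect standard errors are too small and type I error is above the nominal 5%. At the ICC consistent with the article's own power figures the excess is modest, at about 6.7%, with standard errors about 7% too small. It becomes serious only if the ICC is near .05 or above.

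The size rests on an assumed ICC common to both arms, equal cohorts of 10 completers, one time point and no baseline covariate. The direction rests only on a positive ICC and on reading site as the two clinical sites. The documents do not support the unconditional statement that error rates will exceed 5%, nor that the excess will be large.

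**What to change.** In the Data analysis section for Aims 2 and 3, state that:

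- each model includes a random effect for cohort (site by enrollment period, 8 levels) in addition to the within-subject structure, with site kept as a fixed effect;
- the arm effect is tested on between-cohort degrees of freedom, 5 with arm and site or 4 if arm-by-site is retained, by a small-sample method named in advance (for example between-within or Kenward-Roger), including what is done if the cohort variance is estimated as zero;
- the estimated cohort ICC is reported for each outcome.

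If within-site was meant as within-cohort, the same edit settles it.

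No new data or added enrolment is needed. The cost is wider intervals and a revised Power analysis section, which should state the assumed ICC and give power on the cluster-based degrees of freedom that the chosen model leaves. With 8 cohorts, the existing claim of .80 at .67 SD and .92 at .8 SD would have to be lowered.
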